## Abstract

**Background:**

Functional neurological disorder (FND) is a common cause of neurological symptoms including seizures and movement disorders. It can be debilitating, is associated with high health and social care costs, and can have a poor prognosis. Functional magnetic resonance imaging (fMRI) has suggested FND is a multi-network disorder. Converging evidence suggests that other mechanisms including dissociation, interoception, and motor agency may be abnormal in people with FND. Psychedelics are currently under investigation for numerous neuropsychiatric disorders and have been shown to disrupt functional brain networks. Administering psychedelics to people with FND will help us to probe mechanistic theories of the disorder.

**Protocol:**

In this open-label neuroimaging study, we will administer 25mg oral psilocybin with psychological support to people with chronic FND (target n = 24). Participants will undergo resting-state and task-based (Libet’s clock, a measure of motor agency) fMRI sequences which will be compared in a pre-post manner. Additional mechanistic outcomes including measures of interoception (heartbeat tracking task), somatisation, illness perceptions, suggestibility, and dissociation will be collected. Data on expectancy, preparedness, and subjective experience of the psychedelic experience will also be gathered. Participants will be followed up for three months following psilocybin administration. fMRI changes in networks will be analysed using seed-based approaches, and additional exploratory analysis of resting-state imaging will take place.

**Discussion:**

The study will help us to probe the mechanisms thought to potentially underpin FND. As the first modern study of psychedelics in FND, it will also help us to understand whether psychedelic administration alongside psychological support might be safe and feasible in this patient population.

## Introduction

### Background

Functional neurological disorder (FND) produces a range of neurological symptoms and signs which have specific characteristics that positively separate them from those caused by neurological diseases and which implicate a specific malfunction of movement and perception
^
1
^. Common phenotypes include functional motor disorders and functional seizures
^
2
^.

FND is common
^
3–
5
^, with up to 100,000 in the UK living with the disorder
^
6
^. Disability is similar to other neurological disease
^
7
^. Symptoms are often found to persist or worsen over time
^
5
^, and prognosis can be poor
^
8,
9
^. Inpatient healthcare costs alone of FND in the United States are estimated to be around $1.2 billion per year
^
10
^. A large survey of people with FND indicated that only 15% were able to work full-time
^
11
^.

Current best-available treatment options are psychological therapies (such as cognitive behavioural therapy), psychoeducation, physiotherapy, and multidisciplinary rehabilitation, however these are not always effective
^
5,
12,
13
^. Although pharmacological therapies are not frequently used, there are specific cases in which psychoactive compounds may be effective as a single dose, particularly when used to augment psychological or physical therapy, for example in therapeutic sedation for functional dystonia
^
14
^ and historical cases of drug-facilitated abreaction
^
15
^.

### Mechanistic evidence in FND

Functional neurological symptoms are varied, and their expression is likely to be underpinned by complex mechanisms. It may be that functional motor symptoms and functional seizures have distinct pathophysiological mechanisms; nevertheless, the two very commonly co-occur, indicating possible shared propensity mechanisms. Examples of overarching theoretical models of FND include aberrant predictive processing
^
16,
17
^, the integrative cognitive model
^
18
^, and altered emotional processing
^
19
^.

Neurobiological theories of FND have been supported by neuroimaging
^
20,
21
^. People with FND have shown altered connectivity in brain regions such as the motor cortex
^
22–
25
^, medial prefrontal cortex (mPFC)
^
22,
26,
27
^, dorsolateral prefrontal cortex (dlPFC)
^
26,
28
^, inferior frontal gyrus
^
24,
29
^, insula
^
24,
25,
27,
29–
33
^ posterior cingulate cortex
^
34
^, temporoparietal junction (TPJ)
^
25,
35
^, anterior cingulate cortex
^
31,
33,
36
^. Other neuroimaging studies have shown altered activation in regions such as the mPFC
^
37
^, anterior cingulate cortex
^
38
^, and inferior frontal gyrus
^
39
^, and insula
^
40
^. Recently, some authors have suggested that the default mode network (DMN) is particularly implicated in FND
^
32,
41
^.

FND is also associated with impaired sense of agency. Agency refers both to the subjective feeling of volitional control one’s body, as well as the ability to enact such control
^
42
^. Research incorporating an agency paradigm (Libet’s clock test) has indicated that people with FND have a decreased awareness of the intention to move (motor agency) in comparison to healthy controls; attention to intention relative to attention to movement was associated with increased activity in the bilateral inferior parietal lobes, dlPFC-inferior frontal gyrus and pre-supplementary motor area-dlPFC
^
42
^, In addition, replicated functional imaging studies in FND have found hypofunction of the right TPJ, a key node in the network proposed to underpin agency
^
42–
46
^.

Dysfunction of interoceptive processing may also contribute to the generation of functional symptoms
^
47
^. People with FND may have poorer interoceptive awareness than healthy controls, as shown via interoceptive tasks such as heartbeat tracking
^
48–
52
^. Difficulties with interoceptive processing may be a correlate of the disorder or may represent a means by which symptoms arise via aberrant interpretation of somatic signals.

Finally, dissociation may be an additional mechanisms by which symptoms arise
^
49
^. Dissociation can refer to the subjective feeling of disconnect from the self, others, or the environment (also known as depersonalisation and derealisation). It also has an additional specific definition as a psychological model which describes the splitting off of conscious awareness from attention
^
53
^. In FND, this may manifest with the feeling of loss of volitional control over a neurological function.

### Current psychedelic research

Classical psychedelics are agonists or partial agonists at the serotonin (5-HT) 2A receptors which induce states of acutely altered consciousness
^
54
^. Prior to the 1970s, psychedelics were successfully investigated for a number of neurological and psychiatric indications
^
55–
57
^. A resurgence of research interest in psychedelics in recent years has led to investigation in neuropsychiatric disorders such as treatment-resistant depression
^
55
^, headache disorders
^
58,
59
^, anorexia
^
60
^, post-traumatic stress disorder
^
61,
62
^, alcohol use disorder
^
63
^, tobacco addiction
^
64
^, existential distress in life-threatening disease
^
65
^, and obsessive-compulsive disorder
^
66
^. Psychedelics may have ‘cross-diagnostic potential’, and could target core elements of a shared psychopathology across neuropsychiatric disorders, including FND
^
56
^.

Contemporary psychedelic research has emerged within an environment of lingering cultural stigma as well as premature and unjustified hype about their medical efficacy
^
67,
68
^, however well-designed trials are attempting to address these issues
^
69
^. Safety data from these trials is reassuring
^
57,
70
^, and psychedelic drugs have been shown to be physiologically non-toxic and non-habit forming
^
55,
71,
72
^.

Modern psychedelic research involves non-directive psychological support
^
55,
56,
73,
74
^, in which the therapeutic relationship between participant and therapist is thought to be of central importance
^
75
^. This follows three phases: preparation, support during dosing and post-dose psychological integration
^
74
^. At doses of 25mg psilocybin, participants may have transient psychologically-challenging experiences
^
76
^, however psychological preparation is argued to help mitigate these
^
77
^, and post-dose integration helps to process the experience and build upon insights gained
^
78
^.

### Mechanistic effects of psychedelics

5-HT
_2A_ receptors are densely distributed across the cerebral cortex, particularly in association cortices, with relatively scant expression in subcortical regions
^
79
^. There have so far only a few primary neuroimaging studies with psychedelics
^
80
^. Nevertheless, functional neuroimaging studies have shown indications of changes in within- and- between-network-connectivity in canonical brain networks including the DMN
^
81
^. (85) The response to psychedelics (acute and longer-term) are likely to be mediated by multi-network changes
^
82
^.

Psilocybin may lead to network disintegration and desegregation in the acute phase
^
83
^. Post-administration effects on resting state connectivity have shown heterogeneity, however may incorporate increase connectivity within the default mode network
^
84
^, with concurrent increases in inter-network connectivity
^
85,
86
^.

Psychedelics have been shown to exert significant changes on the acute sense of body ownership
^
87,
88
^. Although direct research on psychedelic and agency is scarce, psychedelic users have been shown to have agency related measures which are no different to healthy controls
^
88
^. Similarly direct research analysing the effects of classical psychedelics on interoception is lacking, however the psychoactive compound salvinorin-A has been shown to modify interoception
^
89
^. Randomised trials of 3,4-Methylenedioxymethamphetamine (MDMA)-assisted psychotherapy for treatment of chronic posttraumatic stress disorder showed non-significant reductions in dissociative experiences in the treatment arms
^
90
^.

### Psychedelics in FND

Previous authors have suggested FND, including motor symptoms
^
91
^, and seizures
^
18
^ could representa target disorder for psychedelics
^
57,
92
^. Systematic reviews of ‘pre-prohibition’ case series of patients with FND administered psychedelics such as psilocybin and lysergic acid diethylamide (LSD) have found that side effects were minimal and transient in this population
^
93,
94
^. Nevertheless, as all relevant studies were conducted with insufficient experimental designs, further modern feasibility work is required.

In an international survey of people with FND, self-reported physical side-effects from recreational psychedelic use (n=10) were minimal at worst, and 46% of the >1,000 respondents reported that they would be willing to take part in medically-supervised psychedelic studies, with a further 20% undecided
^
95
^.

### The proposed study

Taken together, this evidence suggests that psychedelics may target some of the mechanistic processes which underpin FND. Administering the psychedelic psilocybin to people with FND will allow us to probe theories of FND which postulate that it is a disorder typified by altered network connectivity across brain networks. Using a pre-post design, we will be able to test whether impaired sense of agency, changes in interoception, and dissociative phenomena are modifiable pathophysiological features of the disorder.

## Protocol

### Aim

The purpose of this study is to investigate the functional neuroimaging response to a single dose of psilocybin in patients with functional neurological disorder.

The study is pre-registered on clinicaltrials.gov (NCT05723276). The study and all relevant documents have ethical approval from the Health Research Authority Research Ethics Committee (23/WA/0213).

### Objectives

We will administer a single 25mg oral dose of psilocybin in people with functional neurological disorder. This dose has been chosen as it is the most commonly-used in contemporary psychedelic trials
^
96
^, is sufficient to induce a recognisable but manageable acute psychedelic effect at a fixed dose
^
97
^, and evidence from other disorders indicates it has been more effective in comparison to lower doses
^
98
^. Participants will undergo functional resting-state and task-based (Libet’s Clock Test) fMRI one day prior to and one week following the psilocybin administration.

Exploratory objectives include assessment of the effect of psilocybin administration on mechanistic targets including interoceptive ability, dissociative phenomena, illness perceptions and self-compassion.

### Endpoints

**
*Primary endpoints*
**

The primary endpoint of this study will be change in functional connectivity functional resting-state imaging via within-subjects region of interest connectivity analysis using a priori seed regions (medial prefrontal cortex, subgenual anterior cingulate cortex, posterior cingulate cortex, insula, temporo-parietal junction) and task-based magnetic resonance using Libet’s clock test. Additional exploratory functional neuroimaging analysis will likely take place with other methodologies (e.g. measures of modularity, entropy).

**
*Exploratory endpoints*
**

1. To assess any changes in the following outcomes following psilocybin administration (pre-post design):a. Interoceptive accuracy and confidence (as per the Heartbeat tracking task and the Multidimensional Assessment of Interoceptive Awareness – Version 2)b. Dissociation (Multiscale Dissociative Inventory Scale)c. Imaginative suggestibility (Creative Imagination Scale)d. Illness perceptions (Brief Illness Perceptions Questionnaire)e. Somatisation tendencies (Somatoform Dissociation Questionnaire)To explore the association of primary and exploratory outcomes with other measures, including:
*i.* Expectancy (as per the Stanford Expectations of Treatment Scale)
*ii.* Psychedelic preparedness (as per the Psychedelic Preparedness Scale)
*iii.* Acute psychedelic experience intensity (as per the Ego Dissolution Inventory and the 5-Dimensional Altered States of Consciousness Rating Scale)
*iv.* Self-compassion (as per the Self-Compassion Scale)
*v.* Personality structure (as per the Short Assessment of Personality Scale)2. To explore correlations of functional MRI connectivity with clinical outcomes (via the Clinical Global Impression; CGI) and assessment of associated symptoms (via the Revised Fibromyalgia Impact Questionnaire; FIQR).3. To explore participants views on acceptability on psychedelic administration with psychological support via qualitative interviews.

## Hypotheses under investigation

Hypothesis 1: Network connectivity from seed regions implicated in FND (including the medial prefrontal cortex, dorsolateral prefrontal cortex, inferior frontal gyrus, insula, posterior cingulate cortex, anterior cingulate cortex, and temporoparietal junction) will be altered post psilocybin.Hypothesis 2: Changes in in other mechanistic markers, including motor intentionality, interoception, dissociation, imaginative suggestibility, and somatisation will be observed.Hypothesis 3: There will be improvement in the FND core and associated symptom severity as measured by the CGI and FIQR.Hypothesis 4: Qualitative interviews will suggest acceptability for this form of therapy. Themes which emerge from these interviews will include changing relationships to their disorder, increased self-compassion, and meaningful experiences engendered by trial participation.

### Study design

This study will be an open label within-subjects design in up to 24 participants (target 20 completers) who have a diagnosis of FND as per Diagnostic and Statistical Manual of Mental Disorders (5
^th^ Edition) (DSM-5) criteria
^
99
^. They must have failed to respond to an FND-specific treatment (such as CBT, physiotherapy, or multidisciplinary rehabilitation).

Within the confines of the sample size, a representative sample of motor and seizure subtypes will be sought for inclusion:

Functional seizures: 10 ± 3 completersFunctional motor disorder 10 ± 3 completers

The sample will also seek to be representative of selected protected characteristics (gender, sexual orientation, and ethnicity) based on FND and population rates see
Table 1.

**Table 1. T1:** Recruitment targets by protected characteristics.

	*UK*	*London*	*Average*	Study target

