### Sample size calculation

We will recruit up to 24 participants for this study. The primary aim of the study is to assess resting-state and task-based functional neuroimaging changes. Based on a previous fMRI study of the effect of psilocybin on resting-state connectivity obtained by fMRI, a mean response in connectivity in the default mode network (a connectivity network of interest) of 2.48 (arbitrary units) and a standard deviation of 2.60
^
84
^ was found in pre versus post psilocybin within-subjects analysis; this signifies an anticipated minimum detectable effect size of 0.95. For a two-tailed test and an alpha of 0.01 (to account for multiple testing) and with a power of 0.90, a total sample size of n=20 is required. An additional four participants will be recruited given expected dropouts.

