### Analysis

**
*Statistical measures*
**

Pre-post changes analysed using paired t-tests. Alpha will be set at 0.05. Any clinical data will be presented descriptively without comparison. Multiple comparisons will be post-hoc corrected.

**
*Qualitative analysis*
**

Free text transcriptions from the qualitative interviews will be thematically analysed. Each transcript will be independently coded by two researchers. The agreed codes will be aggregated using NVivo 14.0. An inductive method will be employed to establish emergent themes from the codes. Coverage (% of total data) for each theme will be calculated.

**
*Functional neuroimaging*
**

Analysis of the neuroimaging data will take place using the KCL Neuroimaging Network and the Rosalind cluster. fMRI analysis will be carried out within Statistical Parametric Mapping software using a seed-based approach implemented in the CONN-fMRI Functional Connectivity toolbox. For each seed we will conduct a seed to voxel analysis using permutation-based multiple comparisons correction at the cluster level as implemented within the CONN toolbox with white matter and CSF (but not grey matter) regressors. The primary analysis will not include global signal regression.

Resting state region of interest connectivity analysis will be performed using a priori seed regions (medial prefrontal cortex, dorsolateral prefrontal cortex, inferior frontal gyrus, insula, posterior cingulate cortex, anterior cingulate cortex, and temporoparietal junction.). Additional exploratory functional neuroimaging analysis may take place with other methodologies (e.g. measures of modularity, entropy).

**
*Libet clock task*
**

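### The pre-post tests ignore the motor/seizure subtype used to shape recruitment; a subtype covariate and descriptive change by subtype would be a cheap improvement

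*Protocol article*

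**What the plan says.** The Study design section of the protocol article states that "a representative sample of motor and seizure subtypes will be sought for inclusion", within the limits of the sample size. The targets are 10 ± 3 completers with functional seizures and 10 ± 3 with functional motor disorder, out of 20 target completers. The stated purpose is representativeness, and the same section sets targets for ethnicity, gender and sexual orientation on the same ground.

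The introduction (Mechanistic evidence in FND) says "It may be that functional motor symptoms and functional seizures have distinct pathophysiological mechanisms; nevertheless, the two very commonly co-occur". The rest of that sentence takes the co-occurrence as a sign of possible shared mechanisms.

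Under Analysis, Statistical measures, the rule is "Pre-post changes analysed using paired t-tests". Under fMRI correlates, the Libet contrast also goes into a paired-sample t-test of pre against post. Neither uses subtype. Nor is subtype among the measures that the Endpoints section lists for association with outcome.

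The sample size rests on one overall effect: a mean change of "2.48 (arbitrary units) and a standard deviation of 2.60", of which the protocol says "this signifies an anticipated minimum detectable effect size of 0.95".

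**The concern.** Subtype is the one clinical feature used to shape the sample, and the introduction accepts that it may matter for mechanism, yet the stated group-level tests do not use it. Two things follow if the subtypes change by different amounts. First, the difference between their means is counted as residual variation, so the pooled test has less power than a test that removes it. Second, the pooled mean is weighted by whichever mix is recruited, and the targets allow anything from 7:13 to 13:7 among 20 completers. Without estimates by subtype, a reader of a positive or a null pooled result cannot tell whether it describes both groups or mainly one. That matters because the study's hypotheses concern FND as a whole.

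**Working it through.** **1. The plan's own figure.** Inputs from Sample size calculation: mean change 2.48, SD 2.60, two-sided alpha 0.01, power 0.90. The effect is d = 2.48/2.60 = 0.954. For a paired t-test with n = 20, the noncentrality is d√n = 0.954 × 4.472 = 4.27 on 19 df, and the exact power is 0.905 (0.902 with d = 0.95). At n = 19 it is 0.883. So the statement "with a power of 0.90, a total sample size of n=20 is required" reproduces exactly for a pooled effect.

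**2. How a subtype gap enters.** Let the within-subtype SD of change be 1 and the gap between subtype mean changes be g. At 10:10 the SD seen by the pooled test is about √(1 + g²/4). The subtype-adjusted test uses the within-subtype SD of 1, on n − 2 df. The documents give no g, so it is varied.

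| Gap g | Pooled SD | Effective d (0.954/SD) | Completers for 90% power, pooled |
|---|---|---|---|
| 0 | 1 | 0.954 | 20 |
| 0.5 | 1.031 | 0.925 | 21 |
| 1.0 | 1.118 | 0.853 | 24 |
| 1.91 | 1.382 | 0.690 | 35 |

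**3. Power at 10:10 with the mean change held at 0.95 SD** (simulation, n = 20). Alpha 0.01 is the sample-size level. Alpha 0.05 is the level under Statistical measures, before any correction.

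| Gap | Pooled, 0.01 | Adjusted, 0.01 | Pooled, 0.05 | Adjusted, 0.05 |
|---|---|---|---|---|
| 0 | 0.904 | 0.901 | 0.981 | 0.981 |
| 0.5 | 0.889 | 0.901 | 0.978 | 0.981 |
| 0.9 | 0.846 | 0.899 | not run | not run |
| 1.0 | 0.833 | 0.900 | 0.965 | 0.981 |
| 1.91 | 0.604 | 0.900 | 0.897 | 0.981 |

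The last row means that one subtype does not change and the other changes by twice the planned effect. A separate run with no gap gave 0.902 pooled and 0.898 adjusted, so the lost degree of freedom costs about 0.4 percentage points. The adjusted test kept its 1% type I error.

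**4. When the average effect itself falls** (10:10, alpha 0.01).
- One subtype at 0.954 and the other at half that (0.477): the mean is (0.954 + 0.477)/2 = 0.716; power is 0.605 pooled and 0.628 adjusted.
- One subtype at 0.954 and the other at zero: the mean is 0.477; power is 0.184 pooled and 0.263 adjusted. Most of the loss comes from the halved mean, which no covariate restores.

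**5. The recruited mix** (only one subtype changes, by 0.954; alpha 0.01).
- It supplies 13 of 20 completers: the mean is 0.954 × 13/20 = 0.620; pooled power is 0.380.
- It supplies 7 of 20: the mean is 0.954 × 7/20 = 0.334; pooled power is 0.073.

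Both mixes lie within the stated targets.

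**6. What subtype estimates can show.** The 95% CI half-width at n = 10 is t(0.975, 9)/√n = 2.262/3.162 = 0.72 SD. A formal comparison of subtypes at alpha 0.05 has power 0.185 for a gap of 0.5 SD and 0.563 for 1.0 SD. It reaches 80% only at about 1.33 SD (10:10) or 1.39 SD (7:13).

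**The case against.** The strongest case against is that nothing here is an error. The hypotheses and the sample size address FND as a whole, no subtype hypothesis is stated, and an average over a mixed sample is a legitimate target. Second-level covariates, subtype summaries and rules for classifying mixed cases are commonly left to an SAP or full protocol, and neither is shown. The gap is assumed, and at 0.5 SD the loss is about one percentage point. All of this stands, and it limits the point to an improvement.

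A reader might infer that the plan imposes rigid quotas because the subtypes differ in mechanism, and then ignores that reason. The text does not support this. The numbers are targets to be sought, with a ±3 margin, for representativeness, and the introduction's remark on mechanism points both ways. The targets are not contradictory either: their lower limits sum to 7 + 7 = 14, which leaves room for up to six mixed or other presentations among 20 completers.

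The covariate also has limits. If the subtypes changed equally in opposite directions, the true average would be zero and the adjusted test would reject only at its nominal 1%. In the 1.91 SD case it raises the chance of a significant overall mean from 0.60 to 0.90 although only one subtype changed. A mean-centred covariate also leaves the average weighted by the recruited mix. So the covariate protects precision, and only the estimates by subtype protect interpretation.

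What survives is that the article does state its group-level test, that this test omits a variable the study already recruits on, and that including it costs almost nothing.

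**Conclusion.** The point holds as a low-cost improvement to the stated analysis. The pooled paired t-test is valid for the average change in FND, and the planned n = 20 is correct for it. Its weakness is conditional. With the mean change held at 0.95 SD, a 10:10 split and alpha 0.01, pooling costs about 1 point of power at a gap of 0.5 SD, 5 points at 0.9 SD and 30 points at 1.9 SD. If only one subtype changes, by 0.95 SD, adjustment moves power only from 0.18 to 0.26, and what is gained is mainly a clearer reading of the result.

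These figures assume that the planning SD of 2.60 is the within-subtype SD, that this SD is equal in both subtypes, and that a single connectivity measure is tested, as in the protocol's own calculation. At alpha 0.05 the losses are smaller.

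A reader might also infer that the plan will report one subtype's change as a finding about FND. The documents do not say so. It is a risk of interpretation that estimates by subtype would reduce.

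**What to change.** 1. At screening, and so before any scan is analysed, record one dominant subtype for each participant and note mixed or other presentations. This also makes the recruitment targets countable.
2. Enter subtype as a mean-centred second-level covariate in the pre-post models for the resting-state and Libet analyses. Centring keeps the intercept as the overall mean change, so the primary question is unchanged.
3. Report mean change with a 95% CI for each subtype, descriptively and with no formal subtype test. Word the conclusions so that a pooled result is not attributed to FND as a whole if one subtype drives it.

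If an SAP or full protocol already provides for this, a sentence saying so is enough.

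Cost: one field at screening, and one degree of freedom in the model, worth about 0.4 percentage points of power if there is no gap. The subtype intervals will be wide, at about ±0.72 SD with 10 participants, and should be presented as such. The sample size need not change.
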